### Randomization, allocation concealment and blinding

3.6

Centralized randomization is performed using a specialised website on the day before surgery. A computer-generated permuted-block randomization list with varying block sizes (ratio 1:1, block size of 2 and 4) was implemented on the website at the beginning of the ELA-study by an independent data manager. The block size is unknown to the investigators. The investigator enters data online regarding each patient to enable inclusion, and the treatment randomly assigned to the patient is immediately provided to the investigator by the website. The allocation ratio is 2:1 (interventional: conventional groups), and the randomization is stratified by age (> or <70 years) and cancer (yes/no). The allocation ratio and the stratification are the same as in the ELA study.

Patients and outcome assessors (neuropsychologists) are blinded to the treatment allocated.

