### Outcome measures

3.8

The primary outcome is the incidence of POCD within 72 hours after major non-cardiac surgery under general anesthesia. A cognitive assessment is performed the day before surgery (baseline) and within 72 hours after surgery using a battery of validated neuropsychological tests (see below) during a face-to-face interview with a trained neuropsychologist. To avoid potential underestimation of the cognitive status, the evaluation is conducted in a quiet environment, after checking for the absence of uncontrolled pain, hypoglycemia, or dysnatremia. The cognitive assessment includes 7 neuropsychological tests that explore 6 different cognitive domains:1.the global cognitive functioning using the Mini-Mental State Examination (MMSE)^[21]^ and the Mattis Dementia Rating Scale,^[22]^2.attention, using the Trail Making Test, part A (TMT-A),3.executive function, using the Trail Making Test, part B (TMT-B) and Stroop tests,4.verbal fluency, using the Isaacs Set Test (IST),^[23]^5.learning and episodic verbal memory, using the Memory Impairment Screen (MIS) test,^[24,25]^6.a psychomotor task using the crossing-off test.^[26]^

According to the method described by Moller et al,^[1,3]^ a Z-score value will be calculated for each neuropsychological test as follows: Z-score = (X1–X2)/SD; where X1 and X2 are the score values obtained at baseline and at the 2^nd^ assessment respectively; and Standard deviation (SD) is the SD of the test performed in an age-matched control population who did not undergo surgery or general anesthesia. The SD observed in the control population is known for all tests used. A composite Z-score value will be calculated as the mean of the Z-scores of all tests.

POCD is defined as a Z-score value >1.96 for at least 2 different tests or a Z-score composite value >1.96.

Secondary outcomes are the differences in the score obtained on each test between baseline and post-surgery assessment.

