### Sample size calculation

3.11

The difference in primary outcome between groups will be compared using Pearson's Chi-squared test, based on an intention-to-treat analysis. Based on the data from the ISPOCD1 study,^[1]^ the expected rate of POCD in the conventional group is 26%. We assume that the expected rate of POCD in the interventional group (closed-loop infusion of propofol and remifentanil) is 10%. Considering a loss to follow-up rate of 5%, a total sample size of 204 patients was calculated (68 patients in the conventional arm, 136 patients in the interventional arm), on a final analysis using the Pearson's Chi-squared test (2-sided, power 80%, alpha 0.05) using the SAS software, version 9.4 (SAS Institute, Inc.).

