### Statistical analysis

3.12

The difference in primary outcome will be compared using Pearson Chi-squared test, based on per-protocol analysis. The per-protocol population is defined as any patient who undergoes the 2 assessments of the cognitive function, that is, at baseline and within 72 hours after surgery. No interim or subgroup analysis is planned.

The normality of the distribution of continuous variables will be tested by using the Shapiro–Wilk test. Intergroup comparisons will be conducted by using the Mann–Whitney *U* or Student *t* tests for quantitative variables, depending on the distribution of data, and using Fisher exact test or the Chi-squared test for qualitative variables.

A logistic regression will be performed to model the risk of POCD including variables with a *P* value of <.20 in the univariate analysis and the treatment allocated.

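### The secondary cognitive comparisons forgo baseline adjustment and the primary test ignores the randomisation strata: a loss of efficiency, not of validity

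*Protocol article*

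**What the plan says.** **Secondary outcomes.** Section 3.8 (Outcome measures) states: "Secondary outcomes are the differences in the score obtained on each test between baseline and post-surgery assessment". Section 3.12 (Statistical analysis) gives one rule for continuous data. After a Shapiro–Wilk test, groups are compared by Mann–Whitney U or Student t "for quantitative variables, depending on the distribution of data". Neither test takes a covariate, and no adjusted model is given for the secondary outcomes.

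**Primary outcome.** Section 3.12 states: "The difference in primary outcome will be compared using Pearson Chi-squared test, based on per-protocol analysis". Section 3.11 (Sample size calculation) names the same test.

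**Strata.** Section 3.6 states that "the randomization is stratified by age (> or <70 years) and cancer (yes/no"), as in the parent ELA study. This gives four cells.

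**Adjusted analysis.** Section 3.12 adds: "A logistic regression will be performed to model the risk of POCD including variables with a" univariate P value below .20, together with the allocated treatment. Only treatment is sure to be in that model.

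**The concern.** Each patient has a baseline score on every test, and age group and cancer status are recorded at randomisation. The stated comparisons make little use of either.

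For the secondary outcomes, subtracting the baseline amounts to fixing its regression slope at 1. When the correlation between the two assessments is below 1 and the SDs are equal, that slope is too steep and the difference carries avoidable noise. If the arms differ at baseline by chance, part of that gap also stays in the change score through regression to the mean.

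For the primary outcome, stratified allocation balances the arms on age and cancer. An unstratified test does not credit that balance, so its variance estimate is somewhat too large if the strata predict POCD.

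At stake are precision on every secondary cognitive score and a little power on the primary.

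**Working it through.** **1. The plan's own figure.** Inputs from section 3.11: POCD rates of 26% (conventional) and 10% (interventional), two-sided alpha 0.05, power 80%, 5% loss. The 2:1 ratio is in section 3.6. For Pearson's test with pooled variance and no continuity correction, the pooled rate is (0.26 + 2×0.10)/3 = 0.1533 and

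n(conventional) = [1.96·√(0.1533×0.8467×1.5) + 0.842·√(0.26×0.74 + 0.10×0.90/2)]² / 0.16² ≈ 63.5, rounded up to 64.

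Then 64/0.95 = 67.4, rounded up to 68. Doubling gives 136 and the total is 204, so the stated size reproduces. With 68×0.95 = 64.6 evaluable conventional patients, power is 80.6%.

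**2. Secondary outcomes: change score against ANCOVA.** Assume equal SDs (set to 1) at both assessments, a linear relation and correlation r. The article gives neither SDs nor r, so r is shown as a range.

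- Change-score variance: 2(1−r)
- ANCOVA residual variance: 1−r²
- Ratio: (1−r²)/[2(1−r)] = (1+r)/2

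The power columns use an illustrative true difference of 0.3 SD (not a figure from the article) and 64.6 against 129.2 evaluable patients.

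| r (assumed) | Change variance | ANCOVA variance | Ratio | Power, change | Power, ANCOVA |
|---|---|---|---|---|---|
| 0.5 | 1.00 | 0.75 | 0.75 | 50% | 62% |
| 0.7 | 0.60 | 0.51 | 0.85 | 72% | 79% |
| 0.8 | 0.40 | 0.36 | 0.90 | 88% | 91% |

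The ratio is also the share of patients needed for equal precision, so the saving is 25%, 15% and 10%.

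**3. Chance baseline imbalance.** With about 65 and 129 evaluable patients, the standard error of a standardised baseline difference is √(1/65 + 1/129) = 0.15. A gap above 0.2 SD in either direction then has a probability of about 19% on any one test (0.2/0.152 = 1.31). Given a gap d, the change-score comparison carries an expected error of (1−r)d. For d = 0.2 that is 0.10 SD at r = 0.5 and 0.04 SD at r = 0.8. ANCOVA removes it if the relation is linear.

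**4. Primary outcome: Pearson against Cochran–Mantel–Haenszel (CMH).** Simulation with about 194 evaluable patients, 2:1 within each of four strata, and 40,000 trials per setting. The stratum shares (45% older, 50% with cancer) and the odds ratios for POCD are assumptions. Power is for 26% against 10%; type I error is with both arms at 26%.

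| OR age / cancer | Power, Pearson | Power, CMH | Type I, Pearson | Type I, CMH |
|---|---|---|---|---|
| 1.5 / 1.2 | 81.8% | 82.0% | 0.049 | 0.050 |
| 2 / 1.5 | 81.8% | 82.4% | 0.045 | 0.048 |
| 3 / 2 | 82.3% | 83.6% | 0.040 | 0.049 |
| 4 / 2 | 82.8% | 84.7% | 0.040 | 0.050 |

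**5. Does the planned logistic model cover the strata?** Suppose both factors are put through the P<.20 screen, with four equal strata and 26% against 10%. At odds ratios of 3 and 2, age enters in about 89% of simulated trials and cancer in about 62%. Entry is likely for a strong factor but not assured.

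**The case against.** - **The primary gain is close to nil.** This stands. Power rises by 0 to 2 points, and nothing in the article shows how strongly age or cancer predicts POCD. The strata were inherited from a study of one-year mortality.
- **An adjusted analysis is already planned.** This stands in part. The logistic regression may well bring the strata in, so it would be wrong to infer that the plan discards them. What remains is that data-driven screening decides their entry and that the model is not the named primary analysis.
- **A difference outcome does not exclude adjustment.** True: regressing the change score on arm and baseline gives the same treatment estimate as ANCOVA on the post-surgery score. The sentence on quantitative variables also does not name the secondary outcomes. Still, it is the only comparison stated for data of this kind, and it has no covariates. Applying it to the secondary outcomes is an inference, but a reasonable one.
- **Change scores match the primary definition and are unbiased under randomisation.** Both are correct. A reader might infer from step 3 that the secondary comparisons are biased by regression to the mean. They are not: the error in step 3 is conditional on an observed gap, averages to zero over randomisations, and is already covered by the variance of the unadjusted test.
- **The 10% to 25% rests on assumed inputs.** This stands. The formula needs equal SDs and a linear relation, and it does not describe the Mann–Whitney route.

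**Conclusion.** The point holds as one of efficiency. Its main part is the secondary outcomes. Under equal SDs and r between 0.5 and 0.8, all assumed, baseline adjustment cuts the variance by 10% to 25% with data already being collected. Section 3.5 places the first assessment after randomisation. It is nevertheless made before surgery by a blinded neuropsychologist on blinded patients, so it can serve as a covariate.

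The primary part is minor. A reader might infer that an analysis that ignores the strata makes the primary p-value invalid. The article does not support that. Pearson's type I error stays at or below about 5%, and falls to about 4% only if the strata are strongly prognostic (assumed odds ratios of about 3 and 2). Nor does anything here call for a new sample size, since 204 reproduces for the stated test. No size can be put on any harm from choosing the test by Shapiro–Wilk, so that is not a separate fault; a method fixed in advance simply makes the switch unnecessary.

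**What to change.** **Secondary outcomes.** Analyse each post-surgery score (or, equivalently, each change score) by ANCOVA with arm, baseline score, age stratum and cancer. For skewed timed scores, name in advance which tests will use a rank-based or robust version. This replaces the Shapiro–Wilk switch.

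**Primary outcome.** Either use a Cochran–Mantel–Haenszel test over the four strata, or force age stratum and cancer into the planned logistic model whatever their P values. Report a risk difference with 95% CI and keep Pearson as a sensitivity analysis. Use the strata as recorded at randomisation.

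**Cost.** No new data and no change to the 204 patients. Because Pearson is named in both sections 3.11 and 3.12, the primary change needs a small amendment to the protocol as well as the SAP. As inclusions began in February 2013, it should be dated and settled before allocation is unmasked for analysis. If an amendment to the primary test is judged not worth a gain of 0 to 2 points, the ANCOVA change is worth making by itself.

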### Laboratory measurements

3.9

Preoperative creatinine, blood glucose, natremia, and kalemia measurements are at the discretion of the anesthesiologist in charge of the patient and will be recorded when available.

Blood creatinine, blood glucose, natremia, and kalemia are measured on the day of the second assessment of the cognitive function to ensure absence of confusion, which may lead to an overestimation of the primary outcome.

### Safety

3.10

All serious adverse events are collected and reviewed by the principal investigator and reported to the trial sponsor (CHU Besancon, Besancon, France) and to the Pharmacovigilance Department of Our Institution. Study insurance has been contracted for all participating subjects by the trial sponsor (CHU Besancon, Besancon, France).

Since no serious adverse event related to patient participation is expected in this study, no independent data safety monitoring committee has been established.

### Sample size calculation

3.11

The difference in primary outcome between groups will be compared using Pearson's Chi-squared test, based on an intention-to-treat analysis. Based on the data from the ISPOCD1 study,^[1]^ the expected rate of POCD in the conventional group is 26%. We assume that the expected rate of POCD in the interventional group (closed-loop infusion of propofol and remifentanil) is 10%. Considering a loss to follow-up rate of 5%, a total sample size of 204 patients was calculated (68 patients in the conventional arm, 136 patients in the interventional arm), on a final analysis using the Pearson's Chi-squared test (2-sided, power 80%, alpha 0.05) using the SAS software, version 9.4 (SAS Institute, Inc.).

### Statistical analysis

3.12

The difference in primary outcome will be compared using Pearson Chi-squared test, based on per-protocol analysis. The per-protocol population is defined as any patient who undergoes the 2 assessments of the cognitive function, that is, at baseline and within 72 hours after surgery. No interim or subgroup analysis is planned.

The normality of the distribution of continuous variables will be tested by using the Shapiro–Wilk test. Intergroup comparisons will be conducted by using the Mann–Whitney *U* or Student *t* tests for quantitative variables, depending on the distribution of data, and using Fisher exact test or the Chi-squared test for qualitative variables.

A logistic regression will be performed to model the risk of POCD including variables with a *P* value of <.20 in the univariate analysis and the treatment allocated.

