### Study outline

3.5

Eligible patients are screened during the anesthesia consultation and receive all information relating to the study by phone before hospital admission. Written informed consent is obtained the day before surgery by investigators after oral explanation of the study before inclusion. After written informed consent is obtained, patients are randomized.

After randomization, a first cognitive assessment is performed by a neuropsychologist blinded to the treatment allocation, using a battery of validated neuropsychological tests (see below).

Patient characteristics, past medical history including ASA physical status, and preoperative blood glucose, sodium, potassium and creatinine levels are collected. The prescription of oral premedication is at the discretion of the anesthesiologist in charge of the patient; any treatment prescribed is also recorded.

On arrival in the operating room, standard monitoring (General Electric Healthcare) is put in place. A dedicated indwelling venous catheter is inserted in a forearm vein and connected to an infusion pump via a 3-way Smartsite (Alaris Medical Systems, San Diego, CA), with a priming volume of 0.3 ml. The BIS electrode (Zipprep, Covidien, Mansfield, MA) is positioned on the patient's forehead and connected to either an A-2000 XP (version 3.11) BIS monitor (Covidien) or a BIS Module (version 4.0 XP, GE-Healthcare, Helsinki, Finland). All patients receive intravenous anesthesia with a medical device enabling calculation of effect-site concentrations of anesthetics. A standard computer is used to provide a user interface and to control communication with the BIS monitor and with both propofol and remifentanil infusion pumps (Alaris) via an RS232 serial port (Infusion Toolbox 95w version 4.11 software (Department of Computer Science, Faculty of Medicine, Université Libre de Bruxelles, Brussels)). The protocol for general anesthesia depends on the treatment allocated by randomization, that is, closed-loop (intervention group) or manual (conventional group) target-controlled infusion of propofol and remifentanil guided by BIS monitoring (see below). With the exception of propofol and remifentanil delivery, the anesthetic protocol is at the discretion of the anesthesiologist in charge of the patient.

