Surgical and anesthetic details are recorded, including: type and duration of surgery; intraoperative blood loss and urine output, blood transfusion, total volume of fluids infused; type and total dose of drugs administered; and all blood pressure, heart rate and pulse oximetry values measured from induction of anesthesia to discharge from the operating room. All data concerning BIS monitoring and propofol and remifentanil delivery are extracted from the computer connected to the BIS monitor and to the propofol and remifentanil infusion pumps. Post-operative pain management and assessment is recorded.

A second cognitive assessment is performed by a neuropsychologist blinded to the treatment allocation within 72 hours after the end of surgery, using the same battery of validated neuropsychological tests as during the first evaluation (see below). If the patient refuses to participate in the second cognitive assessment, the consent is considered to be withdrawn, and the patient is excluded from the study.

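### The primary test is assigned to intention-to-treat in section 3.11 and to a completer set labelled per-protocol in section 3.12, and section 3.5 excludes patients who refuse the second assessment under either label

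*Protocol article*

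**What the plan says.** Three sections of the protocol article decide who enters the primary analysis.

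- Section 3.11 (Sample size calculation) says the primary outcome is "compared using Pearson's Chi-squared test, based on an intention-to-treat analysis".
- Section 3.12 (Statistical analysis) says: "The difference in primary outcome will be compared using Pearson Chi-squared test, based on per-protocol analysis". It then defines the set: "The per-protocol population is defined as any patient who undergoes the 2 assessments of the cognitive function", meaning at baseline and after surgery.
- Section 3.5 (Study outline) says that if a patient refuses the second assessment, "the consent is considered to be withdrawn, and the patient is excluded from the study".

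Randomization comes before both assessments (section 3.5), so every exclusion for a missing assessment happens after randomization. Section 3.11 allows for 5% loss to follow-up. The article gives no reasons for refusal, no expected refusal rate beyond that 5%, and no handling of a missing second assessment other than exclusion.

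**The concern.** Two consecutive sections fix different populations for one confirmatory test. Both statements are affirmative and current, so a fuller protocol or analysis plan could agree with only one of them. Until they are reconciled, the population could be settled after results are known.

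The label is also misleading. Readers expect a per-protocol set to be restricted to patients treated as allocated. This one restricts nothing about treatment and only requires that the outcome was measured.

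Correcting the label would not be enough, because the rule in section 3.5 removes refusers whichever label is used. What is missing is a cognitive test battery in the same 72-hour window in which cognitive dysfunction is the endpoint. If patients with POCD decline it more often, the observed incidence and the power fall. If they do so to a different extent in the two arms, the comparison is biased.

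**Working it through.** **The plan's own figure.** Inputs from section 3.11: 26% (conventional) against 10% (interventional), two-sided alpha 0.05, power 80%, 5% loss. Section 3.6 gives 2:1 allocation. With pooled variance and no continuity correction, the mean rate is (0.26 + 2 × 0.10)/3 = 0.1533 and

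n(conventional) = [1.96 × √(0.1533 × 0.8467 × 1.5) + 0.8416 × √(0.26 × 0.74 + 0.10 × 0.90/2)]² / 0.16² = 63.5, rounded up to 64.

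Dividing by 0.95 gives 67.4, rounded up to 68. So 68 + 136 = 204, which matches the article.

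**Power under either label.** Power = Φ[(difference − 1.96 × s0)/s1], where s0 is the pooled and s1 the unpooled standard error. All 204 patients: 82.5%. With 5% lost (204 × 0.95 ≈ 194): s0 = 0.0549, s1 = 0.0606, power 81%. The sample size supports either reading.

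**Power if refusal depends on POCD, equally in both arms.** The refusal rates are assumptions: r1 among patients with POCD, r0 among the others. The observed rate is p(1 − r1)/[p(1 − r1) + (1 − p)(1 − r0)]. For example, with r1 = 20%, r0 = 2% and p = 0.26: 0.208/(0.208 + 0.7252) = 22.3%.

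| r1 vs r0 | Observed rates | Power |
|---|---|---|
| 5% vs 5% | 26% vs 10% | 81% |
| 10% vs 3% | 24.6% vs 9.3% | 79% |
| 20% vs 2% | 22.3% vs 8.3% | 75% |
| 30% vs 2% | 20.1% vs 7.4% | 71% |

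At 20% vs 2%, overall loss is (68 × 6.68% + 136 × 3.80%)/204 = 4.8%, so a pattern of this kind fits within the planned 5%.

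**Type I error.** Assume no true difference, 3% refusal among patients without POCD, and exact enumeration of the Pearson test at the resulting arm sizes.

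| Refusal among POCD patients, conventional vs closed-loop | True rate 18% | True rate 26% |
|---|---|---|
| 25% vs 25% | 5.1% | 5.1% |
| 5% vs 10% | 5.5% | 5.5% |
| 5% vs 15% | 6.2% | 6.3% |
| 5% vs 25% | 9.7% | 10.8% |

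Last row at a true 26%: conventional arm 0.26 × 0.95/(1 − 0.0352) = 25.6% observed in 66 patients; closed-loop arm 0.26 × 0.75/(1 − 0.0872) = 21.4% observed in 124.

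**Bounds on a result.** Suppose the planned rates appear in completers, with 3 of 68 and 7 of 136 missing (10/204 = 4.9%).

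| Missing second assessments counted as | Conventional | Closed-loop | p |
|---|---|---|---|
| Left out (completers) | 17/65 | 13/129 | 0.003 |
| POCD in both arms | 20/68 | 20/136 | 0.013 |
| POCD in closed-loop arm only (worst case) | 17/68 | 20/136 | 0.072 |

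**The case against.** The two labels differ less than their names suggest. The per-protocol set has no adherence rule, so it moves nobody between arms and removes no crossovers. Refusers leave under both labels. The sets differ only for patients who miss an assessment without refusing, so the scope for choosing a population afterwards is narrow. This stands. It limits the harm but does not remove the contradiction.

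Three stronger readings are tempting, and the documents do not support them.

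- *The completer set depends on the outcome.* The article makes inclusion depend on the outcome being measured. It does not say that patients with POCD refuse more often. Section 3.8 also has testing done in a quiet setting, after checks for uncontrolled pain, hypoglycemia and dysnatremia, which removes some barriers. The link is plausible, but it is an inference.
- *Type I error doubles.* This needs refusal that differs sharply by arm. Patients and neuropsychologists are blinded (section 3.6), and the article offers no mechanism for such a difference. Refusal that depends on POCD equally in both arms leaves the error near 5%.
- *Randomizing before the baseline test biases the comparison.* Section 3.5 does have that order: "After randomization, a first cognitive assessment is performed by a neuropsychologist blinded to the treatment allocation". But a baseline test missed before any anesthesia, in blinded patients with a blinded assessor, cannot reflect a treatment effect. It costs numbers and should cause little bias, so no change of order is asked for.

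It is also fair to say that imputation models are commonly left to an analysis plan. Their absence is not the fault here. The fault is that the article fixes exclusion as the rule.

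**Conclusion.** The point holds as an inconsistency in the primary population together with an exclusion rule that defeats intention-to-treat as written. Nothing else in the article resolves it.

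Its size depends on assumptions that the article cannot settle. With about 5% loss, similar in both arms, the effect on the comparison is small. Steeper refusal among patients with POCD costs up to about 10 percentage points of power over the range shown. Material inflation of type I error appears only at the extreme of the arm-differential range. Even so, a loss of about 5% is enough to move a clear result across 0.05 in the worst case, so the handling of missing second assessments should be fixed before the data are seen.

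**What to change.** - **Sections 3.11 and 3.12:** name one primary population in both, namely all randomized patients analyzed in their allocated arm. Restricting it to those who receive anesthesia would itself be an exclusion after randomization. Call the set with both assessments a completer set and keep it as a sensitivity analysis.
- **Section 3.5:** treat refusal of the second assessment as a missing outcome. Keep the data already collected unless the patient withdraws consent to their use.
- **Missing outcome:** use multiple imputation from arm, baseline test scores and the stratification factors (age and cancer). Imputation from these variables does not by itself correct for refusal that depends on POCD beyond them, so add a sensitivity analysis that counts missing as POCD in both arms.

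The cost is a short amendment to three sections, some extra analysis, and an imputation assumption for about 5% of patients. The sample size and the order of randomization and baseline testing stay as they are.

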## Abstract

**Introduction::**

Post-operative cognitive dysfunction (POCD) is frequent in patients older than 60 years undergoing major non-cardiac surgery, and increases both morbidity and mortality. Anesthetic drugs may exert neurotoxic effects and contribute to the genesis of POCD. The hypothesis of the POCD-ELA trial was that closed-loop target-controlled infusion of propofol and remifentanil could reduce the occurrence of POCD by decreasing the risk of excessive depth of anesthesia and the dose of anesthetic drugs.

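### The only adjusted model picks covariates by a P<.20 screen that does not exclude the trial's own hypothesised mediators, so its treatment odds ratio could be pulled toward 1; the primary test is unaffected

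*Protocol article*

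**What the plan says.** All references are to the protocol article.

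- **Primary test (3.12).** "The difference in primary outcome will be compared using Pearson Chi-squared test, based on per-protocol analysis". Section 3.11 names the same unadjusted test, although it gives a different analysis population; that is a separate matter.
- **Adjusted model (3.12).** "A logistic regression will be performed to model the risk of POCD including variables". Entry depends on one univariate threshold, and treatment is always kept: "value of <.20 in the univariate analysis and the treatment allocated". No candidate list, limit on timing or cap on the number of terms is given. No other adjusted model is described.
- **Stratification (3.6).** Randomisation is stratified by age (split at 70 years) and cancer. Section 3.12 does not say that either factor must be in the model.
- **Data recorded after allocation (3.5).** Patients are randomised the day before surgery. Intraoperative records include "type and total dose of drugs administered; and all blood pressure, heart rate and pulse oximetry values measured from induction" onward, plus all BIS and propofol/remifentanil delivery data.
- **Mechanism (Abstract, Introduction).** Closed-loop delivery is expected to reduce POCD "by decreasing the risk of excessive depth of anesthesia and the dose of anesthetic drugs". The Background repeats the depth pathway.

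**The concern.** Adjusting a randomised comparison for something the treatment itself changes removes the part of the effect that runs through it. Here the article names its presumed mediators, depth and dose, and records both in detail. If the hypothesis is right, both are associated with POCD and so tend to pass a univariate P<.20 screen. They would then sit in the model beside treatment.

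The screen is also a poor way to choose baseline covariates. Each candidate unrelated to POCD has a one in five chance of entry, while a stratification factor can be left out because its univariate P value happened to be large.

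At stake is the treatment odds ratio that this model will produce. Set beside a positive chi-squared result, an attenuated odds ratio could look like a contradiction when it only reflects what was adjusted for.

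**Working it through.** **1. The plan's sample size.** Inputs from 3.11: "the expected rate of POCD in the conventional group is 26"%, "the expected rate of POCD in the interventional group (closed-loop infusion of propofol and remifentanil) is 10"%, two-sided alpha 0.05, power 80%, 5% loss, 2:1 allocation.

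n(control) = [1.96·√((1+1/2)·p̄(1−p̄)) + 0.842·√(p₁q₁ + p₂q₂/2)]² / (p₁−p₂)², with p̄ = (0.26 + 2×0.10)/3 = 0.1533.

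This gives (0.865 + 0.410)² / 0.0256 = 63.5, so 64. Then 64/0.95 = 67.4, so 68, with 136 in the other arm: total 204. The stated "68 patients in the conventional arm, 136 patients in the interventional arm" reproduces. The planned odds ratio is (0.10/0.90)/(0.26/0.74) = 0.32.

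**2. Expected events.**
- All 204 patients: 68×0.26 + 136×0.10 = 17.7 + 13.6 = 31.3.
- After 5% loss: 64.6×0.26 + 129.2×0.10 = 16.8 + 12.9 = 29.7.

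Section 3.6 also mentions a 1:1 ratio. With 102 per arm the count would be 36.7, or 34.9 after loss, which changes nothing below.

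**3. Room for covariates.** At the rule of thumb of 10 events per parameter, 29.7 events carry about 3 parameters including treatment; at 5 per parameter, about 6. The article does not give the number of candidates, so a range is shown. With k candidates unrelated to POCD, 0.2k enter on average, and events per parameter are 29.7/(1 + 0.2k):
- k = 10: 2 enter, 9.9 events per parameter.
- k = 20: 4 enter, 5.9.
- k = 25: 5 enter, 5.0. About 25 is a rough count of the recorded variables that could be offered.

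**4. Effect of a mediator entering.** Simulation with 65 and 129 patients, 1,500 runs per scenario, and marginal POCD rates held at 26% and 10%. One measure is lowered by 1 SD under closed-loop (an assumption), and 10 or 20 noise candidates are added. Every candidate is screened at P<.20 and the logistic model is fitted with treatment forced in. Half mediation means half the full-mediation slope on the logit scale (0.74 against 1.49), with a direct treatment term of −0.50 making up the rest; exp(−0.50) = 0.61. Power is the share of runs in which treatment is significantly protective.

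| Effect carried by the measure | Measure enters | Unadjusted OR; power | OR with the screen; power |
|---|---|---|---|
| None (shifted by treatment, no effect on POCD) | about 50% | 0.32; 0.81 | 0.33; 0.69–0.70 |
| Half | about 100% | 0.31–0.32; 0.82 | 0.60–0.62; 0.18–0.19 |
| All | about 100% | 0.31; 0.81–0.82 | 0.99–1.03; 0.03 |

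**5. Effect of noise alone.** The same runs, keeping the screen and the noise candidates but leaving the treatment-shifted measure out, give an odds ratio of 0.30–0.32 and power of 0.79–0.80. Unadjusted, these are 0.31–0.32 and 0.81–0.82. The damage comes from the mediator, not from the number of noise terms.

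**The case against.** The strongest reply is that this is not the treatment-effect analysis. The primary outcome is tested by an unadjusted chi-squared test. The regression is described only as modelling POCD risk, which fits a secondary risk-factor model with treatment forced in. The article never calls its odds ratio a confirmation, a sensitivity analysis or the trial's effect. This stands, and it limits the point to a secondary result.

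A second reply is that the candidate list may sit in the full protocol or analysis plan, and that recording intraoperative data does not show that they will be offered to the model. This also stands in part. The text supports that mediators are not excluded, not that they will be used. But the entry rule itself is stated, and a univariate P-value screen remains a weak way to choose covariates beside a randomised treatment, whatever the list.

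Three stronger readings are tempting, and the documents do not support them:

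- **That the model is bound to show no treatment effect.** This needs the mediator to enter, to be well measured and to carry the whole effect. The hypothesis does not claim full mediation, and at half mediation the odds ratio is attenuated to about 0.6, not to 1.
- **That blood pressure, blood loss, pain and postoperative laboratory values are mediators too.** Only depth and dose are named as the mechanism. Section 3.9 measures the postoperative laboratory values to rule out confusion.
- **That about 30 events make the treatment estimate unusable through overfitting.** Step 5 of the working shows that noise entry hardly moves it.

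**Conclusion.** The point holds for the secondary model only. As written, the rule admits the trial's own hypothesised mediators and can drop the stratification factors. Its treatment odds ratio could therefore understate the effect.

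The direction, toward 1, follows from the stated mechanism. The size depends on an assumed 1 SD shift and an assumed mediated share: from about 0.31 to about 0.6 at half mediation, and to about 1.0 at full mediation. A measure that treatment shifts but that has no effect on POCD leaves the odds ratio near 0.33 and costs some power.

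The primary P value is not affected. The small event count is a reason to keep the model short, not evidence that its treatment estimate is wrong. The sentence should be changed, but it does not threaten the trial's main conclusion.

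**What to change.** Replace the P<.20 screen in 3.12 with a prespecified supportive logistic model containing treatment, age stratum and cancer. That is 3 parameters, or 29.7/3 = 9.9 expected events each. One baseline cognitive score may be added (29.7/4 = 7.4).

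Exclude every variable measured from induction onward. The cut-off should be worded as pre-treatment rather than pre-randomisation, because 3.5 places the baseline cognitive assessment after randomisation and before surgery.

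If a P<.20-screened risk-factor model, or a model with intraoperative variables, is still wanted, label it exploratory and state that its treatment odds ratio is not to be interpreted as the trial's effect.

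The cost is rewording one sentence, with no new data. The downside is that risk-factor screening becomes exploratory.
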